**4 SAFTY**

Safety will be assessed by the nature, frequency, and severity of adverse events, vital signs, physical and neurological exams, blood and urine collections for clinical labs, and 12-Lead ECGs at the baseline (Visit 1) and over the scheduled visits during the study period. Changes from baseline will be displayed by central tendency, shift tables and marked abnormality. In addition, dropout rates, prior and concomitant medication usage and compliance rates will be calculated.

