**3.2 Inclusion and Exclusion Criteria**

Inclusion criteria：Patients with a definite diagnosis of epilepsy, treated with SRVPA or TPM as monotherapy, between 2 to 75 years old, were enrolled in this study.

Exclusion criteria: epileptic syndromes; only acute symptomatic or non-epileptic seizures; a history of psychiatric or mood disorders; clinically significant laboratory abnormalities, including abnormal liver function, abnormal haematological system function, abnormal kidney function, abnormal endocrine system function, or heart disease; and clinician or the patient feeling that the treatment was contraindicated.

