**3.3 Schedule of Study Assessments for Subjects**

| Study period | | Screen | Visit1 | Visit2 | Visit3 | Visit4 | Visit5 | Visit6 | Visit7 |
| --- | --- | --- | --- | --- | --- | --- | --- | --- | --- |
| Screen by inclusion/exclusion standard | | √ |  |  |  |  |  |  |  |
| Informed consent | | √ |  |  |  |  |  |  |  |
| Demographic information | | √ |  |  |  |  |  |  |  |
| Interrogation and physical examination | | √ | √ | √ | √ | √ | √ | √ | √ |
| Prescribing | |  | √ | √ | √ | √ | √ | √ | √ |
| EEG | | √ |  |  |  |  |  |  |  |
| Safety evaluation | Blood routine examination | IN* | IN | IN | IN | IN | IN | IN | IN |
| Urine routine examination | IN | IN | IN | IN | IN | IN | IN | IN |
| Liver function test | IN | IN | IN | IN | IN | IN | IN | IN |
| Kidney function test | IN | IN | IN | IN | IN | IN | IN | IN |
| ECG | IN | IN | IN | IN | IN | IN | IN | IN |
| Fasting blood sugar test | IN | IN | IN | IN | IN | IN | IN | IN |
| CT or MRI examination | IN | IN | IN | IN | IN | IN | IN | IN |
| Record adverse events described by patients |  | √ | √ | √ | √ | √ | √ | √ |
| Drop-out reason analysis | |  | √ | √ | √ | √ | √ | √ | √ |
| Drug combination judgment | | √ | √ | √ | √ | √ | √ | √ | √ |
| Evaluation | Efficacy |  |  | √ | √ | √ | √ | √ | √ |
| Compliance |  | √ | √ | √ | √ | √ | √ | √ |
| Safety |  | √ | √ | √ | √ | √ | √ | √ |

| Study period | | Visit8 | Visit9 | Visit10 | Visit11 | Visit12 | Visit13 |
| --- | --- | --- | --- | --- | --- | --- | --- |
| Screen by inclusion/exclusion standard | |  |  |  |  |  |  |
| Informed consent | |  |  |  |  |  |  |
| Demographic information | |  |  |  |  |  |  |
| Interrogation and physical examination | | √ | √ | √ | √ | √ | √ |
| Prescribing | | √ | √ | √ | √ | √ | √ |
| EEG | |  |  |  |  |  |  |
| Study period | | √ | √ | √ | √ | √ | √ |
| Safety evaluation | Blood routine examination | IN | IN | IN | IN | IN | IN |
| Urine routine examination | IN | IN | IN | IN | IN | IN |
| Liver function test | IN | IN | IN | IN | IN | IN |
| Kidney function test | IN | IN | IN | IN | IN | IN |
| ECG | IN | IN | IN | IN | IN | IN |
| Fasting blood sugar test | IN | IN | IN | IN | IN | IN |
| CT or MRI examination | IN | IN | IN | IN | IN | IN |
| Record adverse events described by patients | √ | √ | √ | √ | √ | √ |
| Drop-out reason analysis | |  | √ | √ | √ | √ | √ |
| Drug combination judgment | |  | √ | √ | √ | √ | √ |
| Evaluation | Efficacy | √ | √ | √ | √ | √ | √ |
| Compliance | √ | √ | √ | √ | √ | √ |

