| Safety | √ | √ | √ | √ | √ | √ |

| Study period | | Visit14 | Visit15 | Visit16 | Visit17 | Visit18 | Visit19 |
| --- | --- | --- | --- | --- | --- | --- | --- |
| Screen by inclusion/exclusion standard | |  |  |  |  |  |  |
| Informed consent | |  |  |  |  |  |  |
| Demographic information | |  |  |  |  |  |  |
| Interrogation and physical examination | | √ | √ | √ | √ | √ | √ |
| Prescribing | | √ | √ | √ | √ | √ | √ |
| EEG | |  |  |  |  |  |  |
| Study period | | √ | √ | √ | √ | √ | √ |
| Safety evaluation | Blood routine examination | IN | IN | IN | IN | IN | IN |
| Urine routine examination | IN | IN | IN | IN | IN | IN |
| Liver function test | IN | IN | IN | IN | IN | IN |
| Kidney function test | IN | IN | IN | IN | IN | IN |
| ECG | IN | IN | IN | IN | IN | IN |
| Fasting blood sugar test | IN | IN | IN | IN | IN | IN |
| CT or MRI examination | IN | IN | IN | IN | IN | IN |
| Record adverse events described by patients | √ | √ | √ | √ | √ | √ |
| Drop-out reason analysis | |  | √ | √ | √ | √ | √ |
| Drug combination judgment | |  | √ | √ | √ | √ | √ |
| Evaluation | Efficacy | √ | √ | √ | √ | √ | √ |
| Compliance | √ | √ | √ | √ | √ | √ |
| Safety | √ | √ | √ | √ | √ | √ |

* IN = if necessary, which means: laboratory examinations were carried out. Electrocardiogram (ECG) examinations were also performed, if necessary.

If clinical attention was necessary, more visits were scheduled between the regularly scheduled appointments.

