**3.5 Procedures**

The information recorded during the first visit included patient demographics, information about previous antiepileptic treatment, history of febrile seizures, birth traumas, epilepsy in first-degree family members, and neurological diseases (e.g., stroke, head injury, cortical development disorder, or intracerebral infection). A general physical examination and a neurological examination were performed. Laboratory examinations were carried out. Electrocardiogram (ECG) examinations were also performed, if necessary. Surface electroencephalography was performed on each patient to detect significant changes that might contribute to diagnosis. Computed tomography, magnetic resonance imaging and additional examinations, such as thyroid hormones, autoantibodies, and rheoencephalography, were carried out if clinically needed. Clinicians were asked to classify the types of epilepsy, epileptic syndromes, and types of seizures according to the criteria of the ILAE

The patients were asked to return for subsequent reviews at the second week, the first month, the third month, the sixth month and at successive half-year intervals from the date of initial medication. If clinical attention was necessary, more visits were scheduled between the regularly scheduled appointments. To control recall bias, each patient treated at our centres was asked to keep a medical diary with information on seizure onset, combinations with other drugs, adverse events, and hospital admissions. To control the loss of follow-up bias in the case of patients who did not appear for regular visits, follow-up data were obtained through telephone interviews or with structured questionnaire letters by mail. A patient who was lost of contact for more than one year was defined as a follow-up loss.

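### Section 4 plans change-from-baseline laboratory and ECG displays over the scheduled visits, but the schedule makes every such test conditional, so the displays may describe only patients whose clinician chose to test

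*Protocol*

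**What the plan says.** Protocol Section 4 lists among its safety assessments "blood and urine collections for clinical labs, and 12-Lead ECGs at the baseline (Visit 1) and over the scheduled visits during the study period". It attaches no condition to them. It then states the planned presentation: "Changes from baseline will be displayed by central tendency, shift tables and marked abnormality".

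The schedule in Section 3.3 says something different. From Screen to Visit 7 the liver function row reads "Liver function test | IN | IN | IN | IN | IN | IN | IN | IN". Blood routine, urine routine, kidney function, ECG and fasting blood sugar carry the same mark, and it continues through Visit 19. The footnote explains the mark as "IN = if necessary, which means: laboratory examinations were carried out" and then adds that ECGs were also done if necessary. So it defines a conditional mark and in the same sentence says that the laboratory tests took place.

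Section 3.5, in its paragraph on the first visit, says "Laboratory examinations were carried out. Electrocardiogram (ECG) examinations were also performed, if necessary". It gives no rule for repeat laboratory tests or ECGs at later visits. Section 3.2 excludes patients with "clinically significant laboratory abnormalities, including abnormal liver function, abnormal haematological system function, abnormal kidney function", among other conditions.

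**The concern.** A change from baseline or a shift table needs a baseline value and a later value in the same patient. Section 4 reads as if both are collected by schedule. Under Section 3.3 they exist only where a clinician thought the test was needed.

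Tests ordered on suspicion find abnormality more often than tests done by calendar, so the displays would not describe the treated cohort. The drug is chosen by clinician and patient (Section 3.1) and managed as in routine practice (Section 3.4). The person ordering the tests therefore knows the drug and may monitor one drug more closely than the other. A reader who sets the two drugs' shift tables side by side could then see a difference that testing practice created, or miss one that is real.

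The same ambiguity reaches the Screen column. It makes conditional the very tests that would show the liver, blood and kidney abnormalities excluded in Section 3.2, which also sits badly with the unqualified first-visit tests in Section 3.5.

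**Working it through.** The protocol gives no figure on this point. The check is a comparison of passages, followed by an illustration on assumed inputs.

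**1. Count of the schedule.** Columns: Screen plus Visits 1 to 19 = 20. Laboratory and ECG rows: blood routine, urine routine, liver function, kidney function, ECG, fasting blood sugar = 6. Cells: 20 × 6 = 120. All 120 carry the conditional mark and none has a fixed tick.

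**2. Passages side by side.**
- *First-visit laboratory tests.* Section 4: at baseline, unqualified. Section 3.5: carried out, unqualified. Section 3.2: implies some testing. Section 3.3: conditional. Here the schedule is the outlier.
- *Follow-up laboratory tests.* Section 4: over the scheduled visits. Section 3.3: conditional. Section 3.5: silent. The conflict is unresolved.
- *ECG, baseline and follow-up.* Section 4: at baseline and over the scheduled visits. Section 3.3 and its footnote: conditional. Section 3.5: conditional for the first visit. Here Section 4 is the outlier.

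Every change-from-baseline display needs a follow-up value, so each one is touched by the second or third line.

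**3. What selective testing can do to a displayed rate.** Let p be the true share abnormal, s the probability that an abnormal patient is tested, and t the probability that a normal patient is tested. Then

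rate among those tested = p·s / (p·s + (1 − p)·t).

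All inputs are assumptions. Take p = 0.05 on both drugs, with s = 0.80 and t = 0.30 on the first drug:

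0.04 / (0.04 + 0.285) = 0.04 / 0.325 = 12.3%.

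For the second drug:
- Equal monitoring (s = 0.80, t = 0.30): 12.3%, ratio 1.0.
- Closer monitoring of normal and abnormal patients (s = 0.95, t = 0.60): 0.0475 / (0.0475 + 0.57) = 0.0475 / 0.6175 = 7.7%, ratio 12.3 / 7.7 = 1.6.
- Closer monitoring of normal patients only (s = 0.80, t = 0.60): 0.04 / (0.04 + 0.57) = 0.04 / 0.61 = 6.6%, ratio 0.123 / 0.0656 = 1.9.

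The true ratio is 1.0 throughout, and every displayed rate exceeds the true 5%. In the last case the percentages tested are 32.5% and 61.0%. A table of numbers tested would expose that gap; a shift table alone would not.

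**4. Laboratory adverse events over all patients.** Section 4.1 lets laboratory abnormalities count as adverse events. Using the whole ITT population as denominator does not remove the dependence on testing. If 50% of abnormal patients are tested on one drug and 95% on the other (assumed), the detected rates are 0.05 × 0.50 = 2.5% and 0.05 × 0.95 = 4.75%, ratio 1.9. Here the more closely monitored drug looks worse, whereas in step 3 it looks better. The direction cannot be predicted.

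**The case against.** The strongest reply is that clinician-driven testing suits an observational cohort, that Section 4 only displays these data, and that denominators and paired-value rules belong in a SAP, which is not shown. Much of this is fair. Section 3.6.3 plans no between-drug test of laboratory abnormality rates, and the safety outcomes in Section 2.2 are incidences of adverse events. Patient-described adverse events have fixed ticks at Visits 1 to 19, and the primary outcome analysis does not use these displays. But a SAP cannot supply values that were never collected, and it cannot settle which protocol section governs their collection. The conflict is in what this document states.

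Three stronger readings may tempt a reader, and the documents do not support them:
- *Many patients will lack baseline laboratory values.* Section 3.5 states first-visit laboratory tests without a qualifier, and the exclusions in Section 3.2 point the same way. Baseline laboratory data may be complete. Only baseline ECGs are conditional in both the schedule and Section 3.5.
- *The laboratory exclusions cannot be shown to have been applied.* That follows from the Screen column alone and gives Section 3.5 no weight. What stands is that the Screen column disagrees with Sections 3.2 and 3.5.
- *Visit 1 cannot be a baseline because adverse events are ticked there.* Section 4.1 collects adverse events from consent, and consent is ticked at Screen, so that tick is no error.

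It is also true that nothing in the protocol shows monitoring to differ by drug.

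**Conclusion.** The inconsistency is real. It is firm for follow-up laboratory tests and for all ECGs; for first-visit laboratory tests it is confined to the schedule's disagreement with Sections 3.2, 3.5 and 4. If the schedule governs, the planned change, shift and marked-abnormality displays describe clinician-selected patients, and the selection may differ by drug.

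The size and direction of any distortion are unknown. In the scenarios worked here, the false ratio between drugs with identical true rates runs from 1.0 (equal monitoring) to about 1.9. That range rests wholly on assumed testing rates and is neither an estimate nor a bound. The consequence is limited to the laboratory and ECG safety displays and, in part, to laboratory adverse events. The point should be corrected but does not threaten the primary analysis.

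**What to change.** Reconcile Section 4, Section 3.5, the Section 3.3 schedule (including its Screen column, against Section 3.2) and its footnote into one statement of which tests are scheduled and which are conditional. Rewrite the footnote so that the mark has one meaning. Which tests are done, and when, is for the sponsor and investigators; no testing schedule is proposed here.

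If testing stays conditional:
1. Show the number and percentage tested for each assessment, by visit and drug.
2. Limit change and shift displays to patients with paired baseline and follow-up values, and label them as selectively tested.
3. State that no between-drug conclusion will be drawn from central-tendency changes or abnormality rates among those tested.
4. State that laboratory adverse events, even when reported over the ITT population, also depend on who was tested.

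The cost is protocol and SAP wording and one additional table; no procedure is added. The downside is that fewer laboratory and ECG safety statements can be claimed.

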**4.1 Adverse Events, Severity, and Relationship**

Adverse Event (AE): Any untoward medical occurrence in a subject or clinical investigation subject administered an investigational product. An AE does not necessarily have a causal relationship with the medicinal product. For this study the medicinal product is SRVPA or TPM.

All AEs encountered during the clinical study will be reported on the record. All AEs, regardless of relationship to study drug or procedure, should be collected beginning from the time the subject signs the study consent. AEs in clinical investigation subjects include any change in the subject’s condition. This includes symptoms, physical findings, or clinical syndromes.

An abnormal laboratory value may be considered an AE if the identified laboratory abnormality leads to any type of intervention whether prescribed in the protocol or not. It is up to the investigator to determine whether an abnormal laboratory value constitutes an AE. If an abnormal laboratory value is caused by a disease process, the disease process and not the laboratory abnormality should be listed as the AE (eg, if new onset viral hepatitis is causing elevated ALT, hepatitis and not the elevated ALT should be listed as the AE).

Examples of laboratory abnormalities which should be considered as AEs include those which result in withdrawal of the study treatment, withholding study treatment pending some investigational outcome, reduction of dose of the study treatment, or additional concomitant treatment. All laboratory abnormalities considered to constitute an AE should be reported on the appropriate AE page of the record.

Laboratory abnormalities do not need to be listed as separate AEs if they are considered to be part of a clinical syndrome that is being reported as an AE. It is the responsibility of the investigator to review all laboratory findings in all subjects.

Abnormal values should be commented upon as to clinical relevance or importance on the record or the laboratory report as appropriate. Medical and scientific judgment should be exercised in deciding whether an isolated laboratory abnormality should be classified as an AE.

**Every effort must be made by the investigator to categorize each AE according to its severity and its relationship to the study treatment.**

**4.2 Assessing Relationship to Study Treatment**

Temporal relationship of the onset of the event to the initiation of the study treatment

The course of the event, considering especially the effect of discontinuation of study treatment or reintroduction of study treatment, as applicable

Whether the event is known to be associated with the study treatment, or with other similar treatments

The presence of risk factors in the study subject known to increase the occurrence of the event

The presence of non-study treatment related factors which are known to be associated with the occurrence of the event.

**4.3 Classification of Causality**

Not Related: A causal relationship between the study treatment and the adverse event is nota reasonable possibility.

Related: A causal relationship between the study treatment and the adverse event is a reasonable possibility.

**4.4 Intolerable Adverse Events**

Intolerable adverse event include any adverse event leading to treatment failure, such as: event results in death, event is life-threatening (Note: The term “life-threatening” refers to an event in which the subject was at risk of death at the time of the event; it does not refer to an event which hypothetically might have caused death if it were more severe.), event requires inpatient hospitalization or prolongation of existing hospitalization, event results in persistent or significant disability/incapacity, event is a congenital anomaly/birth defect and event leading to SRVPA or TPM withdraw.

**5 REMOVALS OF SUBJECTS FROM THE STUDY DRUG**

In accordance with the Declaration of Helsinki (48th General Assembly, Somerset West, Republic of South Africa, October 1996), subjects have the right to withdraw from the study at any time for any reason. Subjects may be removed from the study for the following reasons:

1. A serious or intolerable AE occurs

2. An intercurrent illness that, in the judgment of the investigator or sponsor, might invalidate the study or place the subject at risk.

3. At the request of the patients, whether economic or other reasons

If the reason for removal of a subject from the study is an AE, the AE and any related test results will be recorded on the record.

**When a subject is removed from the study:** the date of the last dose of study drug and all observations collected up to the time of termination will be recorded on the CRF along with the reason for termination

**6. QUALITY CONTROL AND ASSURANCE**

Before any subjects can be enrolled at a site, an initiation visit will be conducted for study personnel training. The investigator and the full relevant study site staff must be available at this visit. All staff must be trained on study procedures before they conduct any study specific procedures. Following the initiation visit, the study will be monitored approximately every 25 weeks (more when necessary) while subjects are actively enrolled into the study.

**7. ADMINISTRATIVE CONSIDERATIONS**

**7.1 Ethical Conduct of the Study**

The guidelines of the World Medical Association Declaration of Helsinki in its revised edition (48th General Assembly, Somerset West, Republic of South Africa, October 1996), the guidelines of ICH Good Clinical Practice (GCP) (CPMP/ICH/135/95), as well as the demands of national drug and data protection laws and other applicable regulatory requirements, will be strictly followed.

**7.2 Subject Information and Consent**

The investigator will inform the subject of the aims, methods, anticipated benefits, and potential hazards of the study, including any discomfort it may entail. The subject must be given every opportunity to clarify any points he/she does not understand and must be provided with more information if requested. At the end of the interview, the subject may be given time to reflect and can request more time if needed. The subject and/or legal guardian should consent participant into this study.

**7.3 Subject Confidentiality**

If applicable, the guidance set out in the European Directive 95/46/EC will be strictly adhered to when conducting clinical studies.

The subject must be assured that their identity will be protected. To facilitate this, a unique identification code will be assigned by the investigator to each study subject. This will be used instead of the subject’s name and cross-referenced with the subject’s date of birth when reporting AEs and /or other study-related data.

**7.4 Protocol Violations/Deviations**

In general, protocol violations include deviations from inclusion/exclusion criteria, from concomitant medication restrictions, and from any other protocol requirement that could, at least hypothetically, result in significant risk to the subject and/or affect the outcome of the study.

A deviation is defined as non-adherence to the study procedure or schedule as defined by the protocol, or the primary endpoint, that does not place the subject at any added or significant risk or affect the data quality or study outcome. Examples of protocol deviations that do not constitute protocol violations include a missed procedure, an out-of-window study visit, etc. Protocol violations will be noted in the final clinical report.

**7.5 Access to Source Documentation**

The investigator must permit the authorized sponsor, agents of the sponsor, and regulatory agency employees to enter and inspect any site where the drug or records pertaining to the drug are held, and to inspect and copy all records relating to an investigation including subject records.
